### Primary effectiveness aim

#### Aim three

To evaluate the effect of intervention implementation on participant outcomes, specifically incidents of protected sex and proportion of condom use.

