Potential covariates include demographic characteristics; mental health status as measured by the 45-item Brief Symptom Inventory (BSI); history of sexual abuse as measured by the Wyatt Sex History Questionnaire (WSHQ) [55]; and history of physical abuse as measured by the 19-item Revised Conflict Tactics Scale (CTS) [56], which assesses both history and recent (*i.e.* past 90 days) experiences of abuse. Hypothesized mediators [57] include condom use self-efficacy, which has been linked to effective condom use [58,59], as measured by the Condom Use Self-Efficacy Scale [60]; condom communication self-efficacy as measured by a nine-item scale measuring confidence in negotiating the use of a male condom [60]; and couples’ sexual communication skills as measured by a seven-item scale on the level of reported comfort on safer sex communication items [61]. Moderators include several variables identified in Eban I as likely to moderate intervention effects [57]: the length of the couple’s relationship, because those in longer relationships are less likely to practice safer sex [45]; relationship satisfaction will be assessed with the Dyadic Adjustment Scale [62], which asks how partners relate to each other about family finances, time spent together, relational factors, and intimacy; substance use/abuse (frequency and amount of alcohol use each day in the past three months and age of first use) as measured by the CAGE [63] to assess dependence on alcohol, and section B of the NIDA Risk Behavior Assessment (RBA) [64] to assess the frequency, modality, and level of use of licit and illicit drugs in the past month.

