### Specific aim three

We will use repeated measures regression models and multi-level hierarchical modeling [70,71] to evaluate the effect of characteristics of agencies, staff, and couples on the behavioral and psychosocial outcomes. For repeated measures regression models, we will directly incorporate measures into models and deal with intra-class correlations from agency and staff through covariance matrix. With the multi-level nested structure from individuals, couples, agencies, and staff, the hierarchical models will be fitted in three possible steps: (a) to set the foundation for a class of hierarchical models, first we will construct individual-couple-level models with repeated measurements (baseline, post and three-month) within a couple that involves time (and intercept); (b) we will then construct across the couples-level models that involve explanatory variables such as couple demographics; health history; history of alcohol and recreational drug use; HIV/AIDS risk reduction knowledge; perceived couple sexual norms; intervention components, and a binary variable indicating immediate active treatment or wait list control; (c) we will model the regression coefficients obtained from step b at the agency level as functions of explanatory variables of agency characteristics (*e.g.*, organization size and budget, number of staff, etc.). Finally, we will then combine models from steps a, b, and c to form the complete model, which will be estimated through special procedures and software, such as WinBUGS and MlwiN [72,73].

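### The Aim three couple-level model names intervention components beside the randomised arm indicator; with both in, the arm coefficient is not the randomised effect of Eban II and is much less precise

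*Protocol article*

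**What the plan says.** Aim three of the Protocol article is "To evaluate the effect of intervention implementation on participant outcomes, specifically incidents of protected sex and proportion of condom use". Couples are randomised 2:1, 118 to Eban II and 62 to waitlist. Waitlist couples are offered the intervention once the three-month follow-up is complete (Screening and enrollment of couples).

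The analysis is described under Specific aim three in the Data analysis plan. It names two approaches: repeated measures regression and multi-level hierarchical modelling. For the second, "the hierarchical models will be fitted in three possible steps". Step (b) reads "we will then construct across the couples-level models that involve explanatory variables such as couple demographics; health history; history of alcohol and recreational drug use", and the list continues with "HIV/AIDS risk reduction knowledge" and then "perceived couple sexual norms; intervention components, and a binary variable indicating immediate active treatment or wait list control". Steps (a), (b) and (c) are then combined into one complete model. Step (b) is the only place in that section where the arm variable appears.

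The section does not define intervention components. Elsewhere, session attendance and completion are tracked as part of fidelity, dose and intensity (Implementation-focused evaluation), and Table 2 lists core elements session by session.

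**The concern.** Randomisation protects the comparison of arms as assigned. A variable that comes into being after assignment, and that one arm cannot have by design, is a consequence of assignment. Placing it beside the arm indicator splits the treatment effect between two terms, and neither is then the total effect.

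Aim three is the trial's effectiveness aim, and the couple-level sample size rests on a comparison of intervention with waitlist. If the arm coefficient of the complete model were reported as the effect of Eban II, a programme that works could show little or no arm effect, with an interval too wide to be useful.

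**Working it through.** **Inputs from the Protocol article.** Allocation 118 and 62, so the waitlist share is 62/180 = 0.344. Reference effect 0.30 SD (Sample size calculation and power analyses). Eight sessions (The Eban II intervention). The plan gives no figure for the precision of the arm coefficient under this model, so there is none to reproduce. Whether the stated 174 couples is right is a separate question, and nothing below depends on it.

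**Assumed.** Components are coded as number of sessions received, D. D = 0 for every waitlist couple. In the Eban II arm its mean is μ = 6 to 7 and its SD is s = 1 to 2. The protocol gives no attendance distribution. One outcome per couple and a linear model are used to isolate the mechanism; this is simpler than the planned multi-level model.

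**What the arm coefficient estimates.** With D = 0 throughout the waitlist arm, the slope b on D is determined by Eban II couples alone, and

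arm coefficient = (difference in arm means) − b × μ.

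This is the Eban II regression line carried back to zero sessions, minus the waitlist mean. If all Eban II couples receive the same components, s = 0 and the arm and component terms cannot be separated at all.

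**Direction, for a total effect of 0.30 and μ = 6.**
- Effect wholly proportional to dose, b = 0.05: 0.30 − 0.05 × 6 = 0.00. Simulation (3,000 runs, SD 1.5, capped at 8 sessions): 0.00, SE 0.44.
- Dose unrelated to outcome, b = 0: 0.30. Simulation: 0.30, SE 0.44.
- Receipt related to worse outcome, b = −0.2/6: 0.30 + 0.20 = 0.50. Simulation: 0.49, SE 0.43.

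Without the component term, the simulated arm coefficient is 0.30 with SE 0.16.

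**Precision.** The variance inflation factor for arm is

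VIF = 1 + (62/180) × μ²/s².

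| μ | s | VIF | SE multiplied by |
|---|---|---|---|
| 6 | 2 | 1 + 0.344 × 9 = 4.1 | 2.0 |
| 6 | 1.5 | 1 + 0.344 × 16 = 6.5 | 2.6 |
| 7 | 1 | 1 + 0.344 × 49 = 17.9 | 4.2 |

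The unadjusted SE is √(1/118 + 1/62) = 0.157 SD. It becomes 0.157 × 2.02 = 0.32 to 0.157 × 4.23 = 0.66. At s = 1.5 the formula gives 0.157 × 2.55 = 0.40; the simulated 0.44 is higher because capping at 8 sessions narrows the spread.

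**Power, from precision alone.** Take a design with nominal 80% power at two-sided 0.05 (the plan does not state sidedness), so effect/SE = 1.96 + 0.84 = 2.80. Suppose the coefficient stayed at 0.30. At the low end, 2.80/2.02 = 1.38 and power is Φ(1.38 − 1.96), about 28%. At the high end, 2.80/4.23 = 0.66 and power is about 10%.

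**Knowledge and norms.** A covariate unaffected by arm, as any baseline value is, leaves the simulated arm coefficient at 0.30 with SE 0.15 against 0.16. A post-baseline variable assumed to carry one third of the effect gives 0.20. Which case applies depends on the time point, which is not stated.

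**The case against.** The strongest reply is that step (b) is not the treatment-effect analysis. The Abstract assigns the impact of treatment to the waitlist design and the effects of agency and couple characteristics to the multi-level model. Specific aim three opens with a similar purpose. A second approach is named: "For repeated measures regression models, we will directly incorporate measures into models and deal with intra-class correlations from agency and staff through covariance matrix". No covariates are listed for it. The step (b) list is introduced as examples and the steps are called possible.

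Much of this stands, and it limits what may be said.
- A reader might infer that this is the only Aim three model, or that every arm estimate will carry the component term. The text supports neither.
- A reader might infer that knowledge and norms are mediators being adjusted away. They are listed with demographics and history. The protocol says "Hypothesized mediators [57] include condom use self-efficacy, which has been linked to effective condom use", and the other named mediators are condom communication self-efficacy and sexual communication skills; knowledge and norms are not among them.
- A reader might infer that the estimate must shrink toward zero. That depends on the sign of b.
- The figures depend on reading components as a session count, which the protocol does not say.

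The reply does not dispose of the component term. It is expressly named beside arm and carried into the complete model, and no model without it is designated for the effectiveness estimate. The repeated measures text does not define an arm contrast. The point concerns a stated choice, so it is not a detail left to an unseen analysis plan. The logic also holds for any coding of components that is zero throughout the waitlist arm.

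**Conclusion.** The point holds for intervention components. While the waitlist is untreated, a model containing both that term and the arm indicator does not estimate the randomised effect of Eban II. It estimates an extrapolation to Eban II couples who received nothing. This follows from the design and needs no assumed figure.

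The size does rest on assumptions: for a mean of 6 to 7 of 8 sessions and SD of 1 to 2, VIF is about 4 to 18 and the SE about 2 to 4 times larger. Bias is toward zero if receipt goes with better outcome, which is the likelier case for a working programme, and away from zero otherwise.

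For knowledge and perceived norms there is an ambiguity to close and no demonstrated error.

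**What to change.** Under Specific aim three, state that the effect of Eban II (arm, by time) is estimated from a model that excludes intervention components, uses covariates at baseline values only, including knowledge and perceived norms, and accounts for clustering by couple and agency.

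Move components to a separately labelled dose-response analysis, and any post-baseline knowledge or norms to a separately labelled mediation analysis. Specific aim two already foresees a dose–response test at agency level, so the idea is not new to the plan.

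The cost is a few sentences. No data collection changes and no planned question is lost. Trial status reports that data cleaning and analysis have not begun, so on that account the change can be made before results are known.

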### Secondary aim

To determine the cost-effectiveness of implementation of Eban II, standard cost-effective analysis will be conducted using health economic analysis approaches. Two-staged models (instrumental variable regression) [74,75] will be applied and implementation costs and potential costs saving through the intervention will be estimated.

## Trial status

Data collection is underway. Data cleaning and analysis have not commenced.

## Discussion

This hybrid implementation/effectiveness study has the potential to illuminate the processes and complexities associated with supporting adoption of an evidence-based program in resource-limited organizations that typically serve underserved, economically disadvantaged individuals. The study’s innovative features include the dynamic wait-listed design [37], the sustainability period (not typically included in implementation trials) [35], the real-world effectiveness conditions under which the intervention is being tested, and the participatory approach to implementation [76]. One of the overarching goals of the study is to ‘dive deep’ into the cultures not only of the organizations but also of their surrounding communities, which have been greatly impacted by HIV and by health disparities in general, especially due to shrinking state and national budgets designated for HIV prevention efforts in these communities. In systematically addressing current community-, organizational-, and client-level complexities with an innovative and partnered design, this study exemplifies the five core values of implementation science: rigor and relevance, efficiency, collaboration, improved capacity, and cumulative knowledge [44].
